Dihydroartemisinin-piperaquine is co-formulated as a film tablet containing 40 mg of dihydroartemisinin and 320 mg of piperaquine phosphate for oral treatment of uncomplicated *P. falciparum* malaria. Dose finding studies in Thailand and Vietnam established the excellent safety and high efficacy of a once daily 3-day regimen of dihydroartemisinin at 4 mg/kg/day [21]. These phase II-type studies were conducted with the currently available non-GMP formulation in the expectation that oral bioavailability of the new GMP formulation will be similar. We will use the new GMP formulation provided by SigmaTau (Italy) in this study. Our study will be part of a phase III multicentre trial involving five studies sites in five African countries.

Piperaquine has a long terminal elimination half-life of approximately 14 days [11]. This might favour an accelerated emergence and spread of resistant parasite alleles, but by acting as a selective filter at time of reinfection [22].

Dihydroartemisinin-piperaquine is an ACT that seems to offer a highly efficacious, safe, well tolerated, simple and affordable treatment option for uncomplicated *P. falciparum* malaria in endemic countries.

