## Outcome measures and sample size.

### End points

#### Primary end point

The primary end point will be the PCR-corrected adequate clinical and parasitological response (PCR corrected ACPR) at day 28.

ACPR is defined as the absence of parasitaemia on day 28 irrespective of the axillary temperature without previously meeting any of the criteria of early treatment failure or late clinical or parasitological failure.

Patients with late asexual parasite reappearance will be considered ACPR if the PCR analysis shows a new infection rather than a recrudescence.

The total treatment failure is defined according to the WHO criteria [25] as the sum of early and late treatment failures (for definitions see chapter 7.3 Treatment failure).

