#### Secondary end points

The secondary end points will be:

1. Crude (PCR uncorrected) adequate clinical and parasitological response ratio at day 28 (PCR-uncorrected ACPR)
2. Cure ratios at days 42, 63, and 84 (PCR-corrected and PCR-uncorrected ACPR)
3. Fever clearance time (FCT)

Fever clearance time will be defined as the time (in hours) from the start of a patient’s treatment to the first consecutive axillary temperature measurements below 37.5°C (body temperature <37.5ºC for at least 48 hours).

1. Asexual parasite clearance time (PCT)

Asexual parasite clearance time will be defined as the time (in days) from the start of a patient’s treatment to 2 consecutive negative blood slides (collected at different days).

1. Gametocyte carrier rates and geometric mean densities (excluding negatives) will be compared on days 7, 14, 28 and 42.
2. Changes of haemoglobin (Hb) concentration from day 0 to days 28, 42, 63, and 84.
3. Safety profiles of the two treatments.
4. Adverse events, vital signs, blood chemistry and haematology, electrocardiogram (ECG) will be monitored and changes in relevant laboratory parameters will be assessed.
5. Rate of PCR-confirmed reinfections
6. Plasma concentration of piperaquine at time of asexual parasite reappearance.
7. Detection of subpatent asexual parasitaemia on day 7 **and day 14**
8. **Assessment of the relationship between *var* gene transcription patterns and late asexual parasite recurrence**

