### Subject Withdrawal from Study

During the study, the following conditions are reasons for stopping the study treatment and/or for excluding the patients from further efficacy assessments:

1. Any treatment failure (including early failures);

2. Withdrawal of informed consent;

3. Use of antimalarial drugs (or antibiotics with antimalarial activity) outside of the study protocol;

4. Persistent vomiting of study drugs on day 0 (at least twice the same dose);

5. Failure to complete the study treatment;

6. Investigator’s request for safety reasons (for example, onset of serious adverse events, necessitating study interruption);

7. Lost-to-follow up: patient cannot be located by day 28.

Patients with one or more of the conditions listed above will have to be followed-up for the safety assessment until day 42.

These reasons for premature withdrawing will be referred to Day 28 (primary evaluation time). The reasons for withdrawing between Day 29 and Day 42 will also be recorded in the study CRF.

A protocol violation occurs when an event happens that does not allow for accurate interpretation of response to treatment.

Patients meeting one of the following criteria will be considered protocol violations but will not be withdrawn from follow-up:

- violation of any eligibility criteria;
- PCR unclassifiable results;
- failure to attend a follow-up visit on Days 0-2 and patient cannot be located within 6 hours of scheduled time;
- failure to attend two consecutive follow-up visits from Day 3 to Day 28 (visits from Day 3 to 28 must take place within 24 hours of the scheduled time).

The violations listed above are not valid reasons for withdrawing the patients from follow-up (both efficacy and safety assessments). On the contrary, the investigator must do his/her best to respect the allowed time windows at every visit, even if a violation occurred at a previous visit (i.e. a previous visit did not take place or occurred outside the allowed time window).

The protocol violations listed above will not be taken into account for establishing patient inclusion in the intention-to-treat population while they will be a reason for excluding the patients from the evaluable population.

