## Statistical Analysis

### Primary end point analysis

The primary analysis will be based on a 97.5% (one-sided) confidence interval (CI) computed on the difference between the 28-day PCR corrected cure ratios (PP population) of the test and the reference treatments, respectively.

In order to claim that dihydroartemisinin-piperaquine is efficacious, the lower limit of the 97.5% confidence interval of the difference between the treatment groups must be >-0.05 and the point estimate for the 28-day PCR corrected cure ratio of dihydroartemisinin-piperaquine must be >0.90%, in the PP population.

All patients withdrawn from the study will be considered as failures in the ITT population (worst-case scenario).

For computing the PCR-corrected cure ratio, the following rules will be applied:

- The patients with reappearing asexual parasitaemia, which are subsequently found to be due to re-infections are considered as treatment success in both PP and ITT populations;
- The patients for whom the PCR analysis is not interpretable (or blood sample unavailable) are considered as treatment failure in the ITT population, but are excluded from the PP population.

Robustness of results for the primary end point will be investigated by using other analyses, such as the survival analysis techniques.

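### Re-infection has no single scoring rule: the late PCR-corrected cure ratios count some censored children as full-length cures, while other sections count the same children as failures or not evaluable

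*Protocol*

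**What the plan says.** The primary end-point definition (Protocol 10.4.1.1) states: "Patients with late asexual parasite reappearance will be considered ACPR if the PCR analysis shows a new infection rather than a recrudescence". Section 12.3.1 repeats this under a lead-in that is not tied to day 28, "For computing the PCR-corrected cure ratio, the following rules will be applied": recurrences "subsequently found to be due to re-infections are considered as treatment success in both PP and ITT populations". The secondary end points (10.4.1.2) use the same response measure later on: "Cure ratios at days 42, 63, and 84 (PCR-corrected and PCR-uncorrected ACPR".

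Section 10.8.2 lists reasons for stopping treatment and/or "excluding the patients from further efficacy assessments". They include any treatment failure and "Use of antimalarial drugs (or antibiotics with antimalarial activity) outside of the study protocol". Re-infection is not listed by name.

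Survival methods are named in 12.3.1 only as a robustness check on the primary end point. For categorical secondary outcomes, 12.3.2.1 plans Fisher's exact test.

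The protocol expects re-infection to differ between arms. The Introduction says "Piperaquine has a long terminal elimination half-life of approximately 14 days", and a secondary objective (9.2) is to estimate the chemoprophylactic effect from PCR-confirmed re-infections.

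**The concern.** A child whose efficacy observation stops at a re-infection can no longer show a recrudescence of the original infection. Scoring that child as cured at day 84 treats a short observation as a complete one. The ratio then depends partly on local transmission, and by a different amount in each arm if piperaquine delays re-infection. The ratios at days 42, 63 and 84 are where recrudescences surfacing after day 28 would appear.

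The protocol also gives more than one score to such a child. Two analysts following different sections could report different late ratios, and different day 28 and day 63 populations, from the same data.

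**Working it through.** **1. The sections side by side**

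*Febrile re-infection on days 4-28.* Late clinical failure (11.3.2.1) needs parasitaemia and fever and has no PCR condition. The child is therefore a treatment failure, meets a withdrawal reason (10.8.2) and receives rescue treatment (11.3.3). Its scores are:

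- success, by the PCR rule in 12.3.1, in both PP and ITT;
- failure, by the rule in the same section that every withdrawn patient is an ITT failure, and by the modified ITT definition (12.2.1), which counts every withdrawal except loss to follow-up as a failure;
- not evaluable at day 28 or 63 if counts stop before that day, because 12.2.3 keeps early stoppers only for PCR-confirmed recrudescence; the same section makes other early stoppers ITT failures;
- possibly out of PP, since 12.2.2 bars other antimalarials. Read literally, that clause would also remove every rescued recrudescence, so its intended reach is unclear.

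*Afebrile re-infection, or uncomplicated febrile re-infection after day 28.* Late parasitological failure (11.3.2.2) is limited to PCR-identified recrudescence, and the fever criterion of 11.3.2.1 stops at day 28. Neither child is a failure, and Table 1 continues smears and genotyping to day 84. No section ends observation here. If an antimalarial is taken outside the protocol, 10.8.2 ends it, 12.2.2 removes the child from PP, and 11.2.2 makes it an ITT failure.

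**2. Size of the overstatement under the success rule**

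The protocol gives no figure for this and no event rates by arm or day, so all rates below are assumptions. Each calculation supposes that observation ends at *every* re-infection, which makes it a ceiling.

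Overstatement at day D = sum over visits v up to D of [net recrudescence first seen at v] x [probability of re-infection by the previous visit].

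Worked example, using the visit days of Table 1: net recrudescence is 10% in both arms, spread evenly over days 14-42 (artemether-lumefantrine, AL) or 14-63 (dihydroartemisinin-piperaquine, DHA-PQP). Re-infection starts on day 14 (AL) or 28 (DHA-PQP) at a constant hazard and reaches 40% or 20% by day 84.

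- AL: 2.5% at each of days 21, 28, 35 and 42. Re-infected by the previous visit: 0, 0.0498, 0.0971, 0.1421. Overstatement = 2.5 x 0.2890 = 0.72 points.
- DHA-PQP: 10/7 = 1.43% at each of seven weekly visits, days 21-63. Re-infected by the previous visit: 0, 0, 0, 0.0275, 0.0543, 0.0803, 0.1056. Overstatement = 1.43 x 0.2677 = 0.38 points.

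Day 63 ratios in this example (net cure 90% in both arms):

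| Rule | AL | DHA-PQP |
| --- | --- | --- |
| Re-infection = success (12.3.1) | 90.7% | 90.4% |
| Re-infected leave the evaluable set (12.2.3) | 87.2% | 89.1% |
| Re-infected = ITT failures (12.2.3) | 62.9% | 78.3% |

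The ITT row is net cure x (1 - re-infected by day 63): 0.90 x 0.6994 and 0.90 x 0.8698. The evaluable row divides this by (1 - share whose first event is re-infection): 0.6294/0.7222 and 0.7828/0.8790.

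Varying net recrudescence (5% or 10%) and day 84 re-infection (AL/DHA-PQP 20/10%, 40/20%, 60/40%, 50/50%):

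- Overstatement at days 42, 63 and 84: AL 0.16-1.24 points. DHA-PQP 0.01-0.12 at day 42 and 0.09-1.09 at days 63 and 84.
- Shift in the difference (DHA-PQP minus AL): -1.15 to -0.15 points at day 42, and -0.41 to +0.13 at days 63 and 84.
- Day 28: 0 to 0.22 points.

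**3. A second model, with later recrudescence in the test arm**

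Lognormal recrudescence times (log SD 0.35), 10% with median day 42 (DHA-PQP) against 5% with median day 24 (AL). Re-infection starts at days 28 and 14. Figures are for day 84.

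| Re-infection hazard per day | DHA-PQP failures, net / as scored | AL failures, net / as scored | Shift in difference |
| --- | --- | --- | --- |
| 0.19% | 9.8 / 9.5 | 5.0 / 4.9 | +0.2 |
| 0.6% | 9.8 / 8.9 | 5.0 / 4.7 | +0.5 |
| 1.5% | 9.8 / 7.8 | 5.0 / 4.2 | +1.2 |

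The first row is set to section 10.5.5, which expects about 50 breakthrough infections, recrudescent and new together, among DHA-PQP patients. Of 250 children, 250 x [1 - 0.902 x exp(-0.0019 x 56)] = about 47 have one. The overstatement is then 0.29 points (DHA-PQP) and 0.11 points (AL).

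At day 42 the same model shifts the difference the other way, by -0.1 to -0.3 points at hazards of 0.6-1.5%. At day 28 the largest overstatement is 0.31 points, in AL. If median test-arm recrudescence is day 28 instead of 42, the day 84 difference moves by about 0.1 point or less.

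**The case against.** The strongest objection is that observation is never said to end at re-infection as such. A reader might infer that every re-infected child drops out of efficacy follow-up. The text does not support that: it is certain only for febrile recurrence on days 4-28, and otherwise depends on danger signs, severe malaria or antimalarial use outside the protocol. This stands, and it makes the figures above ceilings.

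A reader might also infer that the bias helps non-inferiority. The documents do not support that either. The shift ran against the test drug in most scenarios and favoured it mainly when test-arm recrudescences were both more frequent and late. Where the failure rules of 11.2.2, 12.2.1 or 12.2.3 govern instead, the ratios are pulled down, so even the sign is not fixed by the text.

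The efficacy claim rests on day 28 PP alone, the late ratios carry no margin, and PCR-uncorrected ratios at the same days are unaffected by this rule. These points stand and limit the importance.

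The estimator for a secondary end point is often left to an analysis plan. Here, however, the protocol itself fixes the scoring rule and fixes it in conflicting ways, so this is more than detail left for later. Counting re-infection as success is a legitimate definition where follow-up is complete. It fails only where follow-up has stopped.

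**Conclusion.** The point holds in a limited form. The success rule reaches days 42, 63 and 84, and for febrile re-infection on days 4-28 it counts a censored child as a full-length cure. Other sections score some of the same children as ITT failures or as not evaluable, so the late ratios and the day 28 and 63 populations depend on which section governs.

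Under the success rule the late ratios are overstated: about 0.1-0.3 points at day 84 with re-infection set to the roughly 50 expected breakthrough infections, and up to about 1-2 points under heavy re-infection. The arm difference can move in either direction, and the day 28 primary estimate moves by at most about 0.3 points. These sizes rest on assumed event rates and on observation ending at every re-infection. The conflict between rules matters more: in the worked example it spreads the day 63 AL figure from 62.9% to 90.7%. It should be corrected, but it does not threaten the primary conclusion.

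**What to change.** - Reconcile 10.8.2, 11.2.2, 11.3.2.1, 11.3.2.2, 12.2.1, 12.2.2, 12.2.3 and 12.3.1 into one scoring rule for re-infection. For each analysis population, state how a re-infected child counts and on what day its efficacy observation ends. Which children stay under follow-up or are treated is for the trial team to settle; the text only needs to be consistent.
- For days 42, 63 and 84, estimate the PCR-corrected cure ratio by Kaplan-Meier, with recrudescence as the event and re-infection or loss censored on the day found. Give a 95% confidence interval for the arm difference.
- Name the same analysis as the day 28 survival sensitivity analysis that 12.3.1 leaves open.
- Keep the simple proportion as a secondary display.

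The cost is wording only, since visit dates and genotyping are already collected. The small downside is that censoring assumes re-infection is independent of the risk of recrudescence; this assumption should be stated.

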### Secondary end point analyses

#### Secondary efficacy end point analyses

Normally distributed variables will be summarized by calculating means and standard deviations (SD) and compared with parametric tests (unpaired and paired Student’s *t* or analysis-of-variance (ANOVA) tests as appropriate). Non-normally distributed variables will be summarized by median and interquartile ranges (IQR) or geometric means and 95% confidence intervals. Comparisons will be made with nonparametric tests (unpaired and paired Wilcoxon or Kruskal-Wallis rank tests as appropriate). The Fisher’s exact test will be used to assess differences in categorical outcome variables between the cohorts. The statistical significance level will be set to 5%.

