## Secondary objectives:

- PCR-uncorrected day 28 cure ratio;
- Safety profiles of the two treatments;
- Time to asexual parasite clearance (PCT);
- Time to fever clearance (FCT);
- Gametocyte prevalence and density on days 7, 14, 28, 42, 63 and 84;
- Haematological recovery (Haemoglobin (Hb) changes from day 0 to day 28, day 42, and day 84;
- Cure ratios at day 42 (PCR corrected and PCR uncorrected);
- Cure ratios at day 63 (PCR corrected and PCR uncorrected);
- Cure ratios at day 84 (PCR corrected and PCR uncorrected);
- Rate of PCR-confirmed reinfections to estimate the chemoprophylactic effect of dihydroartemisinin-piperaquine;
- Plasma concentration of piperaquine at time of asexual parasite reappearance;
- Detection of subpatent asexual parasitaemia on day 7 **and day 14;**
- **Assessment of the relationship between *var* gene transcription patterns and late asexual parasite recurrence**

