### Sample size calculation

The study is designed as a non-inferiority trial.

The opinion of physicians and experts in malaria treatment has been sought for defining the non-inferiority margin, and this has been set at 5%. In addition, the experts have agreed that, in order for the new treatment to be considered efficacious, its PCR-corrected cure ratio at day 28 should not be lower than 90%. Therefore, in the present trial, dihydroartemisinin-piperaquine will be considered efficacious if both the following conditions are met (see section 2.1):

(i) The PCR-corrected cure ratio at day 28 of dihydroartemisinin-piperaquine is not inferior to the cure rate of artemether-lumefantrine by 5% or more, and independently of the reference drug performance,

(ii) The cure rate of dihydroartemisinin-piperaquine is at least 90%.

In summary, for the non-inferiority analysis, the clinical and statistical specifications for the sample size computations are as follows:

- Primary end point = PCR-corrected cure ratio at day 28.
- Primary analysis = based on 97.5% one-sided confidence intervals for the difference in day 28 cure ratios.
- Alpha = 0.025 (one-sided).
- Power = 80%.
- Cure ratio at day 28 of artemether-lumefantrine = 95% (results from multicentre phase III trial of Coartem in children; [name] personal communication).
- Non-inferiority margin for the difference (test-reference) = -0.05%.
- Analysis will be per-protocol.

To demonstrate non-inferiority of Artekin compared to Coartem the study will require 235 patients per treatment group. To allow for an approximate 5% loss to follow-up rate, 250 patients per treatment group (500 patients in total) will be enrolled in the Kilifi study.

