1. PCR

A blood sample will be collected on filter paper (grade 1) for parasite genotyping.

1. Blood Slide

A thick and thin blood smear will be obtained from the subject to verify the presence of *P. falciparum* and to determine asexual and sexual parasite densities. Thick and thin blood films will be prepared, dried and stained with Giemsa stain according to standard operating procedures.

Parasite density will be calculated by counting the number of asexual parasites per 200 leukocytes in the thick blood film, based on an assumed leukocyte count of 8,000 /µl by light microscopy at 1000x magnification. One hundred high-powered fields (HPF) will examined (independent of presence or absence of asexual parasite stages). The parasite density per µL will be calculated using the following formula: numbers of parasites/µl = number of parasites counted x 8,000/number of leukocytes counted

1. Laboratory Tests

Blood haemoglobin, red blood cell count, total leukocyte count, differential count (neutrophils, basophils, eosinophils, monocytes, lymphocytes) and platelet count.

Total bilirubin, ALT and creatinine will be measured. **Parasite RNA will be analysed for variant gene expression patterns.**

1. Administration of the study drugs

For details see chapter 7 (Investigational product(s) & concomitant medications and non-drug therapies).

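### Haemoglobin change from day 0 falls under a general rule that names only unadjusted tests; adjusting for day 0 haemoglobin would gain precision at no cost (low priority)

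*Protocol*

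**What the plan says.** Section 9.2 of the protocol lists the objective as "Haematological recovery (Haemoglobin (Hb) changes from day 0 to day 28, day 42, and day 84". Section 10.4.1.2 lists the end point as "Changes of haemoglobin (Hb) concentration from day 0 to days 28, 42, 63, and 84". Both therefore define it as a change from baseline, but only the second includes day 63.

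Baseline Hb is available. The day 0 laboratory tests (section 10.5.1.1) start with "Blood haemoglobin, red blood cell count, total leukocyte count", and Table 1 in section 10.5 marks haematology on day 0 for all children.

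The comparison rule is in section 12.3.2.1 and covers secondary efficacy variables in general: "Normally distributed variables will be summarized by calculating means and standard deviations (SD) and compared with parametric tests". The tests named are unpaired and paired t tests or "analysis-of-variance (ANOVA) tests as appropriate". For non-normal variables, "Comparisons will be made with nonparametric tests", meaning Wilcoxon or Kruskal-Wallis. The section does not mention Hb by name, and nowhere does the protocol name a covariate or a baseline-adjusted model.

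**The concern.** Applied to a two-arm comparison of Hb change, the rule in section 12.3.2.1 leads to an unpaired test on the raw difference between follow-up and day 0. Subtracting the baseline fixes its coefficient at 1. If the regression slope of follow-up Hb on day 0 Hb is not 1, part of the day 0 variation stays in the change and adds noise to the arm comparison. With equal SDs the slope equals rho, so this holds whenever rho is below 1. A model with day 0 Hb as covariate estimates the slope and removes that noise.

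What is at stake is the width of the interval, and hence the power, for one secondary end point at three scheduled time points. The data needed to do better are already collected.

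**Working it through.** **Inputs.** The end point (change from day 0), the unadjusted tests and the availability of day 0 Hb come from sections 9.2, 10.4.1.2, 12.3.2.1 and 10.5.1.1. The planned 250 children per arm comes from section 10.4.2. That sample size was set for day 28 cure. The protocol states no SD, correlation, effect or power for Hb, so there is no Hb figure of its own to reproduce, and every Hb quantity below is an assumption shown over a range.

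**Formula.** Let s be the day 0 SD, k·s the follow-up SD and rho their correlation.

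- Variance per child of the raw change: s²(1 + k² − 2·rho·k).
- Residual variance of follow-up Hb given day 0 Hb: s²k²(1 − rho²).
- Ratio of adjusted to change-score variance: R = k²(1 − rho²)/(1 + k² − 2·rho·k).
- With equal SDs (k = 1): R = (1 − rho²)/(2(1 − rho)) = (1 + rho)/2.
- Narrowing of the confidence interval: 1 − √R.

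The factor (1/n1 + 1/n2) cancels, so R depends on neither arm size nor allocation ratio. Estimating one slope costs one degree of freedom, which is negligible with about 500 children. Analyses of covariance of the change and of the follow-up value, each with day 0 Hb as covariate, give the same arm difference, so adjusting does not alter what is estimated.

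**Results.**

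| SD ratio k | rho | R | CI narrower by |
|---|---|---|---|
| 1 | 0.3 | 0.65 | 19.4% |
| 1 | 0.5 | 0.75 | 13.4% |
| 1 | 0.7 | 0.85 | 7.8% |
| 1 | 0.9 | 0.95 | 2.5% |
| 1.2 | 0.5 | 1.44 × 0.75/1.24 = 0.871 | 6.7% |
| 1.2 | 0.7 | 1.44 × 0.51/0.76 = 0.966 | 1.7% |
| 0.85 | 0.5 | 0.7225 × 0.75/0.8725 = 0.621 | 21.2% |

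**Check by simulation.** With 250 per arm, equal SDs and 4,000 runs for each rho, the observed variance ratios were 0.64, 0.74 and 0.86 at rho 0.3, 0.5 and 0.7, against 0.65, 0.75 and 0.85 from the formula.

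**In other units.** With equal SDs, rho 0.5, 250 per arm and a two-sided 5% test, the difference detectable with 80% power is (1.960 + 0.842) × √(2 × 0.5) × √(2/250) = 0.251 SD for the raw change. It is 2.802 × √0.75 × √(2/250) = 0.217 SD after adjustment. Equivalently, the raw-change test would need 250/0.75 = 333 children per arm to match. For an effect that the raw-change test detects with 80% power, the adjusted analysis has power Φ(2.802/√R − 1.960): 93.5%, 89.9% and 86.0% at rho 0.3, 0.5 and 0.7. The 80% is a reference point chosen for illustration. With k = 1.2 the power is only about 85% at rho 0.5 and 81% at rho 0.7.

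**Schedule.** Table 1 marks haematology for all children on days 0, 3, 7, 28, 42 and 84. On day 14 it is conditional on an abnormal day 7 result. Section 10.5.1.8 confirms days 42 and 84 for the later visits. Day 63 has none, although section 10.4.1.2 lists an Hb change to that day.

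**The case against.** The strongest objection is that the protocol never says Hb change will be compared by an unadjusted test. Section 12.3.2.1 is a generic paragraph that leaves the choice to suitability. A paired test of recovery within each arm would also fit it, and the choice of a covariate for one secondary end point is often settled in a statistical analysis plan, which was not at hand. This stands in part: the link to Hb is an inference. However, no other rule in the protocol covers Hb, and the section does not defer. It names the test families, and none is adjusted. The point is therefore about a stated method.

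A reader might also infer that the raw-change test is biased because it over-corrects when the arms differ by chance in day 0 Hb. The documents do not support that. Under randomisation the test is unbiased and keeps its type I error. The shift that a chance imbalance causes is already part of its standard error, so it is the same precision loss seen from another side. A large imbalance is also unlikely. With 250 per arm the standard error of the day 0 difference is √(2/250) = 0.089 SD, so a difference of 0.3 g/dL would be about 2.2 standard errors at an assumed SD of 1.5 g/dL, or 1.7 at 2.0 g/dL.

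Finally, the gain cannot be guaranteed to be material. It depends on rho and on the SD ratio, neither of which the protocol gives. It nearly vanishes as the slope k × rho approaches 1.

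**Conclusion.** The point holds as a low-priority improvement. By inference from the general rule, Hb change would be compared between arms without day 0 Hb, which is valid but less precise than the adjusted analysis of the same data. With equal SDs and rho between 0.3 and 0.7, confidence intervals would be about 19% to 8% narrower after adjustment. With a follow-up SD 1.2 times the day 0 SD, they would be about 7% narrower at rho 0.5 and 2% at rho 0.7. In large samples adjustment is at least as precise, with equality only at a slope of 1. These sizes rest wholly on assumed SDs and correlations. A fixed minimum gain in power should not be read into them. Neither the primary day 28 cure comparison nor its conclusion is touched.

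**What to change.** In section 12.3.2.1, add: Haemoglobin at days 28, 42 and 84 will be compared between arms by analysis of covariance with day 0 haemoglobin as covariate, and the adjusted difference with its 95% confidence interval will be reported. Keep the mean change per arm as a descriptive summary, so that the objective in section 9.2 is still reported in its own terms.

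Limit the sentence to those three days. Wording such as every follow-up day would take in day 63, which has no scheduled haematology, and day 14, when only children with an abnormal day 7 result are tested. Separately, reconcile the day 63 Hb change in section 10.4.1.2 with Table 1, section 10.5.1.8 and the objective in section 9.2.

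The cost is one sentence of analysis text and a slightly less simple model than a t test. The analysis at days 28, 42 and 84 needs no new data or visits.
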